### Mental health status measures

The level of psychological capital will be assessed by the 24-item psychological capital questionnaire (PsyCap-24) [15]. It includes 6 items for each of its 4 components (hope, efficacy, optimism and resilience). Participants will be asked to rate the items using a 6-point scale, ranging from 1 (strongly disagree) to 6 (strongly agree). A higher score indicates higher PsyCap level. The PsyCap-24 has already been translated into Chinese and adapted in a previous Hong Kong study, showing excellent internal reliability (Cronbach’s alpha equals to 0.92) [45].

Well-being will be measured by the Warrick-Edinburgh Mental Well-being Scale (WEMWS) [46] and the Satisfaction with Life Scale (SWLS) [47], both are already available in Chinese. The WEMWS is a 14-item self-rating scale with item scores ranging from 1 to 5. The SWLS only has 5 items, where participants are asked to rate on a 7-point Likert scale, ranging from 1 (strongly disagree) to 7 (strongly agree).

Depressive symptoms will be measured by Centre for Epidemiologic Studies Depression Scale (CES-D) [48,49]. The CES-D includes 20 items, using a 4-point Likert scale (ranging from 0 to 3) to rate individuals’ depressive symptoms. It has been validated in Hong Kong before [50]. Score ranges from 0–60, with higher scores indicating more severe depression. A score of 16 to 26 for CES-D is considered as potential mild depression, and 27 or above as major depression.

### Work engagement and ROI related measures

The Utrecht Work Engagement Scale - shorten version (UWES) [51] will be used to measure engagement. It is a 9-item self-rating scale with item scores from 0 to 6. It has an excellent internal consistency (e.g. Cronbach’s alpha varied between 0.85 to 0.92 across different samples from 10 countries [52]).

Work productivity changes will be measured by the WHO’s Health and Performance at Work Questionnaire - short form (HPQ) [53], which obtains information on individuals’ past 4 weeks productivity through assessing both absenteeism and presenteeism. It is currently unavailable in traditional Chinese. A standard ’translation and back-translation’ process was adopted to translate it into traditional Chinese [54]. We pre-tested the Chinese version before making further improvement.

The other two components for calculating the ROI besides work productivity are medical costs and time costs. To obtain these two measures, participants in both control and intervention groups will be asked to report the past-month medical expenditures and the share paid by their employers (if any); while the intervention group alone will also report time they spend on the entire trainings.

### Demographics and other variables

The demographic information will be collected during the registration. In the post-intervention survey, participants of the intervention group will be asked to report their satisfaction level towards our program; a manipulation check question will also be employed to explore the potential moderation effect between individuals’ self-rated devotion level and other individual-level outcomes. The control group participants, on the other hand, will be asked to report whether they have been exposed to any educational information related to mental health or psychology during the past four weeks.

### Treatment adherence and user experience

Because this is the first on-line positive psychology intervention conducted in Hong Kong and among the few in Asia, we will also evaluate the process to better understand user experience and to test the extent to which treatment is adhered and intervention is successfully implemented. In addition to the self-rated devotion level, we will collect timing and progress information (built in behind the scene as part of the system record), while participants log in every time and move along each training session, answer “check-point questions” and complete “homework”. The amount of “happy coins” itself could serve as another indicator of participants’ level of commitment to the learning experience. As part of the post-intervention assessment, we ask participants to leave open-ended comments. For those who quit the program, we plan to conduct some follow-up interviews to better understand their experience and the reasons behind the drop-out.

### Data analysis

Results will be reported according to the Consolidated Standards of Reporting Trials (CONSORT) statement regarding eHealth [55]. The primary data analysis will follow the intention-to-treat principle and compare the differences in the above outcome measures between the intervention group and the wait-list control group. Because of the potential dropout, missing data is expected. When appropriate, we will use the expectation-maximization (EM) method to impute missing data [56]. In addition, per-protocol analysis will also be conducted.

The two groups will first be described in terms of their baseline characteristics. The primary data analysis will compare the effectiveness of *Happy@Work* in the intervention group with the changes in the control group, based on the differences on PsyCap-24, WEMWS, SWLS, CES-D and UWES. Repeated measures of ANOVA will be used to check the multivariate main effects of intervention (compared with control) and time (pre, post, follow-up), as well as their interaction effect. A two-sided P value of 0.05 or less will be considered as significant. We will compute the standardized effect size (Cohen’s d) as well. Moderator analysis will also be conducted to explore which sub-group/s would benefit more from the intervention, by regressing outcome variables on independent variables like age, gender, education and baseline CES-D scores. Work productivity change will be compared between these two groups as well. SPSS V.18 will be used for the data analysis.

To make the business case for similar type of interventions, return-on-investment of the program will be calculated from the employers’ perspective using the following formula:

ROI = (Gain from investment - Cost of investment)/Cost of the investment;

where, *Gain from investment* = total monetized value of employees’ work productivity gains + savings in employers’ share of medical cost; and

*Cost of investment* = Program designing and operation costs (assuming employers self-fund similar programs) + the monetized time cost (if employees use work time for the program training*).*

Self-reported monthly salary will be used to monetize the work productivity changes and time cost for each individual. All the afore-mentioned items will be the incremental value compared with the control group.

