### Sample size

Based on the existing evidence from PPIs, we expect to find a standard effect size of 0.3 or larger comparing the intervention group with the control group [14]. To achieve a statistical power of 80%, given a two-sided alpha of 0.05, we need at least 177 participants in each condition, i.e. a sample size of 354 or more.

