## Discussion

### Strengths and limitations

To the best of our knowledge, this is the first experimental study that explores the applicability of PsyCap development among Asian population; and it is also one of the few studies that measure improvement in depression and mental well-being as a result of PsyCap development. We will also examine differences in these outcomes between individuals with different level of depressive symptoms. Through the investigation of changes in individuals’ work productivity from absenteeism and presenteeism, our study will be one of the few studies that quantify productivity gains and return-on-investment from any type of mental health promotion.

There are also several limitations that we need to mention. Compared with group based or individual based consultation, although web-based self-administrated interventions are usually cheaper, it might also be less effective. Meanwhile, since we will mainly use self-report method to collect data, this might cause recall bias. The ROI estimation will be less objective compared with those studies that choose one specific company and use the company records (e.g., medical claims, sick leave days) for such calculation. Another limitation would be the possible high dropout rate for this study, despite self-selection and other strategies to reduce it (e.g. email reminders and other incentives). Although studies have found that self-selected people enjoyed more obvious effects than non-self-selected individuals in PPIs [57], this also calls for caution against over-generalizing our results.

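### EM imputation followed by ordinary repeated measures ANOVA carries no imputation uncertainty: it inflates the group-by-time test if arm is in the imputation model, and shrinks the effect if it is not

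*Protocol article*

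**What the plan says.** The Data analysis section of the protocol article makes the primary analysis intention-to-treat and acknowledges incomplete follow-up: "Because of the potential dropout, missing data is expected". The remedy, limited to cases where it is appropriate, is that "we will use the expectation-maximization (EM) method to impute missing data". The test comes next: "Repeated measures of ANOVA will be used to check the multivariate main effects of intervention (compared with control) and time (pre, post, follow-up"), together with their interaction. The threshold is conventional: "A two-sided P value of 0.05 or less will be considered as significant".

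This analysis covers PsyCap-24, the primary outcome, and WEMWS, SWLS, CES-D and UWES. Under Strengths and limitations the article adds: "Another limitation would be the possible high dropout rate for this study". It gives no dropout figure. It also does not state the number of imputations, whether arm is in the imputation model, or any variance correction.

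**The concern.** EM used to fill gaps gives each missing value its predicted mean from the observed visits. Two kinds of uncertainty are then lost: the scatter of real values around that prediction, and the error in estimating the prediction itself. An ordinary ANOVA counts every filled value as an observation with full degrees of freedom.

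The consequence depends on a choice that the article leaves open. If arm is in the imputation model, or EM is run separately by arm, the arm difference is not biased by the fill but its standard error is too small. If arm is left out, dropouts in both arms are predicted from one pooled regression, which pulls the arms together. The first route risks a false claim of effectiveness on the primary outcome; the second understates a real effect. The problem grows with dropout, which the authors themselves say may be high.

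**Working it through.** **Inputs from the article.** Two-sided alpha 0.05 and 80% power ("To achieve a statistical power of 80%, given a two-sided alpha of 0.05"); effect 0.3 SD ("we expect to find a standard effect size of 0.3 or larger"); 177 per arm; four assessments (baseline, post-intervention, 1 month, 3 months); EM imputation; repeated measures ANOVA.

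**Assumptions.** Dropout of 10% to 50%, monotone and completely at random; equal correlation between visits, mainly 0.6, with runs at 0.5 and 0.7; the same effect at each follow-up visit.

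**1. The article's own figure.** n per arm = 2(1.960 + 0.842)²/0.3² = 174.4, so 175 (t version 175.4, so 176). Power at 177 per arm is 0.806. The stated 177 reproduces and is not in dispute.

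**2. What a conditional-mean fill removes.** With k earlier visits observed and common correlation ρ, the variance of a filled value is R² = kρ²/(1 + (k−1)ρ) of the true variance. For ρ = 0.6:
- k = 1: 0.36
- k = 2: 0.72/1.6 = 0.45
- k = 3: 1.08/2.2 = 0.49

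So more than half of the variance of every filled 3-month value is missing.

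**3. Arm in the imputation model, no true effect.** Simulated type I error at nominal 5%, 177 per arm:

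| Dropout | Group × time, ρ = 0.6 (separate simulations) | Group × time, ρ = 0.5 | Group main effect, ρ = 0.6 | Group main effect, ρ = 0.5 |
|---|---|---|---|---|
| 10% | 7.6%, 8.4% | 7.9% | not available | 5.1% |
| 20% | 11.5%, 11.6%, 13% | 12.7% | 5.8% | 6.5% |
| 30% | 16.9%, 17.9%, 18% | 19% | 6.6% | 7.1% |
| 40% | 25.6%, 25.9%, 27% | not run | 7.0% | not run |
| 50% | not run | 40% | not run | about 9.7% |

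At ρ = 0.7 and 30% dropout the group × time figure is 19%. With 1,500 runs the Monte Carlo standard error at a true 5% is √(0.05 × 0.95/1500) = 0.6 points. The same ANOVA on completers only (ρ = 0.5) rejects in 5.3%, 4.9%, 4.5% and 4.2% of null trials at 10%, 20%, 30% and 50% dropout, so the inflation comes from the fill and not from the ANOVA.

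A hand check uses a baseline-adjusted 3-month contrast, which is not a planned test and serves only as illustration. At 30% dropout the mean reported standard error was 0.072 and the true SD of the estimate 0.097 to 0.101. The nominal cut-off of 1.96 then acts as 1.96 × 0.072/0.097 = 1.46 or 1.96 × 0.072/0.101 = 1.40, which gives error rates of about 15% and 16%. The simulated rates were 14% and 15.3%.

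**4. Arm omitted, no true effect.** Group × time type I error is 4.6%, 5.0% and 4.6% at 20%, 30% and 40% dropout (ρ = 0.6), and 5.2%, 4.9%, 4.0% and 4.8% at 10%, 20%, 30% and 50% (ρ = 0.5). The level is held.

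**5. Arm omitted, true difference 0.30 SD.** Each observed visit has regression weight ρ/(1 + (k−1)ρ), and the baseline difference is zero. For ρ = 0.6 the filled 3-month arm difference is therefore approximately:
- baseline only observed: 0
- baseline and post: 0.375 × 0.30 = 0.1125
- baseline, post and 1 month: 2 × 0.2727 × 0.30 = 0.1636

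If dropouts split equally over the three follow-up visits, the average is (0 + 0.1125 + 0.1636)/3 = 0.092. The estimate is then (1 − d) × 0.30 + d × 0.092, that is 0.279, 0.258, 0.238 and 0.217 at d = 10%, 20%, 30% and 40%. Simulation gave 0.28, 0.26, 0.24 and 0.22. A separate simulation at ρ = 0.6 gave 0.25, 0.23 and 0.21 at 20%, 30% and 40%. At ρ = 0.5 the result was about 0.22 at 30% and 0.18 at 50%.

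**6. Does a remedy restore the level?** Multiple imputation including arm (20 sets, combined standard errors) gave type I error of 5.1%, 4.3%, 4.7% and 4.9% for the adjusted 3-month contrast at 10% to 40% dropout. The single fill gave 7.3%, 10.3%, 15.3% and 21.9% on the same contrast. The mixed model was not simulated.

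**The case against.** The strongest case on the other side has four parts.

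- **The 5% level is not always lost.** A reader might infer that any EM fill followed by ANOVA gives standard errors that are too small. The article does not say that arm is in the model, and with arm omitted the level is held. This stands: the inflation is conditional. The other branch does not rescue the plan, because it biases the estimate towards zero.
- **No dropout rate is stated.** A reader might take 20% to 40% as the dropout that the protocol expects. It says only that missing data are expected and that high dropout is possible. The rates above are assumptions. Inflation is already visible at 10%, so the conclusion does not depend on the upper end.
- **Not every planned test is badly affected.** The group main effect, also planned, rises only to about 5-7% up to 40% dropout. The article plans P values and Cohen's d and mentions no confidence intervals, so a charge of wrong intervals would go beyond it. Nor does it say that EM will fill the productivity or cost items, or describe their distribution; a complaint about skewness has no basis in the text. All of this stands.
- **It is a condensed article, and EM is limited to cases where it is appropriate.** Variables, number of fills and variance handling could sit in a fuller document. That a single file is meant is an inference, though it is the natural reading. What the article does fix is a named imputation method followed by a named test, with no alternative and no correction between them. That combination can be judged as written.

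**Conclusion.** The point holds in conditional form. As written, EM imputation followed by repeated measures ANOVA treats filled values as data, and neither version of the imputation model is sound for the primary comparison. With arm included, the group-by-time test, which carries the treatment effect over time, runs at about 8%, 12%, 17-18% and 26% at 10%, 20%, 30% and 40% dropout. With arm omitted, the test keeps its level, but a true 0.30 SD at 3 months is reported as about 0.28, 0.26, 0.24 and 0.22.

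These sizes rest on 177 per arm from the article and on the assumed dropout rates, correlation of 0.6 and random monotone dropout. The direction of each fault did not change in the runs at correlation 0.5, nor did the inflation and the held level at 0.7. The sample size calculation is unaffected.

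**What to change.** In the Data analysis section, replace the EM fill-in and ANOVA with one of these:

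- a likelihood-based linear mixed model for repeated measures, with group, time and group-by-time terms, fitted to all observed visits of every randomised participant; or
- multiple imputation with arm and baseline in the imputation model, the analysis run in each imputed set, and the standard errors combined across sets.

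Either uses the data already planned and keeps the intention-to-treat comparison. The cost is a change of analysis wording. The downside is that intervals will be wider than those from the EM-filled file, because they will reflect the information actually lost to dropout.

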## Methods/Design

### Study design

This study is designed as a two-arm randomized control trial. Upon visiting the intervention website, individuals will complete an initial screening to determine the eligibility. Eligible participants will continue the registration process and the baseline assessment, followed by an automatic randomization process that assigns the eligible participants into one of two groups. The intervention group will receive a 4-week access to *Happy@Work* trainings that develop each of the four PsyCap components. Measurements are scheduled at baseline, directly after the 4-week PsyCap trainings, and at 1 and 3 months follow up. The control group will be on the waiting list for 4 months before they can access the training materials. Figure 1 shows the flow of the study design.

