### Outcome assessment

The primary outcome is the level of psychological capital. The secondary outcomes include well-being, depressive symptoms, work engagement and economic cost-benefit (as measured by work productivity, medical expenditure and time cost for using the website). All these measures are self-reported, and will be collected through the *Happy@Work* website. Assessments will be made at the baseline, immediately after individuals finish the 4-week trainings, and at 1 and 3 months follow-up after the completion. All the measurements, except specified, will be assessed in both control and intervention groups.

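### The primary ANOVA counts the pre-randomisation score as an outcome level and lists two unranked tests of intervention, neither of which is the 0.3 SD contrast used to size the trial

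*Protocol article*

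**What the plan says.** - **Outcome.** Under Outcome assessment: "The primary outcome is the level of psychological capital". On timing: "Assessments will be made at the baseline, immediately after individuals finish the 4-week trainings, and at 1 and 3 months follow-up after the completion". That makes four visits, one of them before treatment.
- **Order of baseline and randomisation.** Under Study design: "Eligible participants will continue the registration process and the baseline assessment, followed by an automatic randomization process".
- **Sample size.** "we expect to find a standard effect size of 0.3 or larger comparing the intervention group with the control group". The error rates are given as "To achieve a statistical power of 80%, given a two-sided alpha of 0.05", and the result is "we need at least 177 participants in each condition, i.e. a sample size of 354 or more". No visit and no model term is attached to the 0.3.
- **Analysis.** Under Data analysis: "Repeated measures of ANOVA will be used to check the multivariate main effects of intervention (compared with control) and time (pre, post, follow-up". The sentence goes on to name the interaction, so the full list of tested terms is "main effects of intervention (compared with control) and time (pre, post, follow-up), as well as their interaction effect". Significance is set at two-sided 0.05 and no term is given priority. The same section describes the primary comparison as one against the change seen in the control arm, and it plans Cohen's d. Baseline PsyCap-24 is not named as a covariate; baseline CES-D appears only in the moderator regressions.

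**The concern.** Because baseline is measured before allocation, the expected arm difference at that level of the time factor is zero. An intervention main effect taken over all levels mixes this zero with the post-treatment differences, so it understates the treatment effect even if the effect never fades.

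The interaction avoids this. With four visits, however, it is a joint test on 3 degrees of freedom: a significant result does not by itself say at which visit, or in which direction, the arms differ.

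Two things are at stake. First, the 80% power was worked out for a comparison that is neither of these terms. Second, with two tests and no ranking, the article does not fix what would count as a positive result on PsyCap-24.

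**Working it through.** **Inputs from the article:** effect 0.3 SD, two-sided alpha 0.05, power 80%, 177 per arm, four visits, baseline before randomisation.

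**Assumptions:** SD of 1 at every visit, one common correlation r between any two visits, no dropout. The article gives no r, so a range is shown.

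**1. The plan's own figure.** n per arm = 2 × (1.960 + 0.842)² / 0.3² = 174.4, so 175; the t-test version gives 176. Power at 177 per arm is 80.6% (normal) or 80.4% (t). The stated 177 is therefore, to within two participants, an ordinary two-sided comparison of two groups at a single measurement, with no repeated measures and no covariate.

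**2. Intervention main effect.** With a constant effect, the four-visit mean difference is (0 + 0.3 + 0.3 + 0.3)/4 = 0.225, which is 25% below 0.3. The SD of a person's four-visit mean is √((1 + 3r)/4). Power = Φ(0.225 / [SD × √(2/177)] − 1.96). At r = 0.5, SD = 0.791, the standard error is 0.0840 and the ratio is 2.68, giving 76% (simulation of 4,000 trials: 76.5%). Averaging exactly offsets the dilution when (1 + 3r)/4 = (0.225/0.3)² = 0.5625, that is r = 0.417.

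**3. Interaction.** The noncentrality is (177/2) × Σ(d − mean d)² / (1 − r). With a constant effect the sum is 0.225² + 3 × 0.075² = 0.0675, so the noncentrality is 5.97/(1 − r), referred to F on 3 and 350 df.

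**4. Baseline as covariate.** The residual SD is √(1 − r²) at one visit, and √((1 + 2r)/3 − r²) for the mean of the three post-baseline visits.

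Power at 177 per arm with a constant 0.3 SD effect:

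| Test | r = 0.3 | r = 0.5 | r = 0.7 |
|---|---|---|---|
| Main effect, four visits | 87% | 76% | 67% |
| Interaction, 3 df | 68% | 83% | 97% |
| Two groups, one visit, unadjusted | 81% | 81% | 81% |
| Baseline-adjusted, one visit | 84% | 90% | 98% |
| Baseline-adjusted, mean of three | 98.9% | 99.2% | 99.9% |

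**5. Sensitivity to a fading effect.** The article does not posit fading; 0.3/0.2/0.1 is an illustration. At r = 0.3/0.5/0.7 the main effect has 54/43/36%, the interaction 54/70/91% and the baseline-adjusted three-visit mean 81/83/92%. A baseline-adjusted comparison at 3 months alone, where the effect would be 0.1, has only 19% at r = 0.5 and 26% at r = 0.7.

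**6. Two unranked tests.** Under the common-correlation assumption the visit mean and the within-person contrasts are independent. If a significant result on either term were allowed to count, the false-positive rate would be 1 − 0.95² = 9.75%. Simulation with 20,000 trials each gave 9.7% at r = 0.5 and 10.0% at r = 0.7.

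**The case against.** The strongest reply is that the plan does not rest on the diluted term. The interaction is named alongside it and fits the stated comparison with change in the control arm. Having baseline as a level is what makes the interaction a test of differential change. It is valid under randomisation, it already draws some precision from baseline, and under a constant effect it exceeds 80% power at r = 0.5 and above. The planned Cohen's d can show direction. All of this stands.

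Three stronger readings are tempting, and the article does not support them:

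- **That the primary analysis is underpowered.** Under a constant effect the main effect falls below 80% only above a correlation of about 0.42, while the interaction is at 68% at r = 0.3 and 75% at r = 0.4. Which term falls short depends on a correlation that is not given.
- **That 177 per arm is wrong.** It reproduces for the comparison it describes.
- **That the error rate is doubled.** This would follow only if either term could count as success. The article neither says so nor rules it out.

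It can also be said that covariates and the exact contrast are commonly left to an analysis plan. That is fair for the choice of visit, and nothing here favours the post-intervention visit over 1 or 3 months. It does not answer the point about what the article does fix: the model, baseline as a level of time, and two tested terms with no order between them.

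**Conclusion.** The point holds in a limited form. The four-visit main effect is not a sound measure of efficacy, because it shrinks a constant 0.3 SD effect to 0.225 SD. The interaction is sound but is an omnibus test. Neither is the contrast for which 80% power was calculated, and the article does not say which decides.

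The dilution follows from the design and needs no correlation, although its size assumes that all four visits enter the time factor. If follow-up were a single level, the average would be (0 + 0.3 + 0.3)/3 = 0.2 SD. The power figures depend on the assumed correlation, equal SDs and no dropout. Under those assumptions, adjusting for baseline at one visit adds about 3 points of power at r = 0.3 and 17 at r = 0.7 over the unadjusted comparison. The sample size needs no change on this account.

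**What to change.** Analyse the post-baseline PsyCap-24 scores with baseline PsyCap-24 as a covariate rather than as a level of the outcome, for example in a mixed model with arm, visit and arm by visit over the three post-baseline assessments. Pre-specify one baseline-adjusted arm contrast as primary: either one post-baseline visit chosen by the sponsor, or the mean of the three. Report it with its 95% confidence interval, and make the remaining visit contrasts secondary. State that the intervention main effect over all four visits will not be used as evidence of efficacy.

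The cost is a change of wording. Baseline PsyCap-24 is already collected, and no further participants or assessments are needed. The small downside is that the sponsor must commit to one contrast before seeing data. That choice matters if the effect fades, since a late single visit would then have much less power than an early one or the three-visit mean.

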### Aims of the research

Our study aims to demonstrate the effectiveness and cost-effectiveness of a psychological capital development intervention (named “*Happy@Work”)* for improving the mental well-being among working population in Hong Kong. Through designing the intervention in an on-line platform customized for local business and social environment, we will investigate the processes by which individuals from the eastern culture may adhere to the treatment and develop PsyCap. Our research will also fill some gaps in the current literature by testing hypotheses raised yet lacking evidence, for example, can the intervention benefit depressed individuals more than non-depressed ones? In addition, we will calculate the ROI of this intervention, intended for the business sector to take further actions.

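### The moderator analysis, as stated, names no group-by-covariate interaction, so it cannot show who benefits more from the intervention

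*Protocol article*

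**What the plan says.** All references are to the protocol article; a statistical analysis plan may exist but is not shown.

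- **Data analysis, aim:** "Moderator analysis will also be conducted to explore which sub-group/s would benefit more from the intervention".
- **Data analysis, method, in the same sentence:** "by regressing outcome variables on independent variables like age, gender, education and baseline CES-D scores".
- **Data analysis, the only interaction in the plan:** the repeated-measures ANOVA examines "main effects of intervention (compared with control) and time (pre, post, follow-up), as well as their interaction effect". This is group by time; no baseline covariate enters it.
- **Aims of the research:** among the hypotheses said to lack evidence, the example given is "can the intervention benefit depressed individuals more than non-depressed ones".
- **Strengths and limitations:** "We will also examine differences in these outcomes between individuals with different level of depressive symptoms".
- **Demographics and other variables:** the term moderation is also used for the relation of self-rated devotion to the individual-level outcomes, an item asked only of the intervention group.

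**The concern.** A moderator is a baseline variable across whose levels the treatment effect differs. To estimate that, a model must contain randomised group and let its effect vary with the covariate. The stated regression lists only baseline covariates. Its CES-D coefficient describes how the outcome varies with baseline depressive symptoms in all participants together, which is prognosis.

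Two errors become possible. A covariate that only predicts the outcome could be reported as identifying those who benefit more. A covariate that does modify the effect could be missed, or be found significant with no way to attribute that to the intervention. The risk is plainest for baseline CES-D, because CES-D is also an outcome and its baseline value can be expected to predict later values in both arms. The question about depressed workers is a declared aim, and no other analysis in the article could answer it.

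**Working it through.** **1. The plan's own figure.** The Sample size section assumes a standardised effect of 0.3, with 80% power at the two-sided 5% level, and concludes: "we need at least 177 participants in each condition, i.e. a sample size of 354 or more". With n per arm = 2(1.960 + 0.842)²/0.3², the result is 175 (176 with the t distribution). Power at 177 per arm is 80.6% (80.4% with the t distribution). The stated 177 reproduces and is not in dispute.

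**2. What the stated regression estimates.** Let T be group (0/1, allocated 1:1), X a standardised baseline covariate, and

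Y = a + bT + cX + dTX + error.

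Moderation is d. Because T is randomised and half of the participants have T = 1, regressing Y on X alone estimates a slope of c + d/2. Adding T as a main effect leaves that slope unchanged. So d cannot be separated from c. The same holds if Y is a change score: c then includes regression to the mean, which occurs in both arms.

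**3. Consequences, by simulation.** Assumptions: 177 per arm, b = 0.3, X and error standard normal, two-sided 5% level, 2,000 replicates, complete data. Entries are the percentage of trials in which the covariate term (first two models) or the product term (last model) is significant.

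| Scenario | c + d/2 | Covariates only, as stated | Group + covariate | Group, covariate and product |
|---|---|---|---|---|
| Prognostic only: c = -0.5, d = 0 | -0.5 | 100% | 100% | 4.7% |
| True moderator, arm slopes cancel: c = -0.15, d = 0.3 | 0 | 4.9% | 5.0% | about 80% |

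The second row is a special case. If instead c = 0 and d = 0.3, the pooled slope is 0.15 with standard error about 1/√354 = 0.053, so t is about 2.8 and the stated model is significant about 80% of the time. But c = 0.15 with d = 0 gives the same pooled slope, so the result could not be credited to moderation.

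**4. What the right test can detect.** For a binary split with share p depressed, the difference between the two subgroup effects has

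SE = √[(2/177)(1/p + 1/(1 - p))],

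and the difference detectable at 80% power is 2.802 × SE. The article does not give the trial's p. The 28% comes from the survey cited in its section on mental health in Hong Kong, a different population; 20% and 50% are assumed bounds.

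| p | SE | Detectable difference (SD) | Power for a 0.3 SD difference |
|---|---|---|---|
| 0.50 | 0.213 | 0.60 | 29% |
| 0.28 | 0.237 | 0.66 | 24% |
| 0.20 | 0.266 | 0.74 | 20% |

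These figures apply to a binary split. For continuous CES-D the product term has SE of about √(1/177 + 1/177) = 0.106, so 2.802 × 0.106 = 0.30 outcome SD per SD of CES-D is detectable. This agrees with the simulated 80%, but it is a different scale from a difference between two subgroups.

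**The case against.** The strongest reply is that this is a condensed description. The analysis is called a moderator analysis, its aim is framed as differential benefit, and the covariate list is left open. Since the list omits even randomised group, the authors may simply have abbreviated a standard interaction model, and the terms of an exploratory model are often left to the analysis plan. This stands in part: a reader might infer that the trial will fit no interaction, and the article does not show that. But the article does state a method, and that method does not deliver the stated aim. The label does not secure the kinder reading either, because elsewhere the article applies moderation to an item asked only of the intervention group, where no contrast with control is possible.

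Other stronger readings also go too far:

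- **The sentence in Strengths and limitations repeats the fault.** It follows a sentence about improvement resulting from the intervention, so it may mean differences in effect. It is ambiguous and proves nothing either way.
- **A real interaction would go unseen.** That holds only when the arm slopes roughly cancel; otherwise the covariate may be flagged but cannot be interpreted.
- **A false moderator is nearly certain.** That depends on an assumed prognostic strength, and on the analyst reading a prognostic coefficient as moderation.
- **The trial's main result is at risk.** The moderator analysis is separate from the primary comparison, and its wording is already exploratory.

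**Conclusion.** The point holds for the method as written: it estimates prognostic association and cannot say whether depressed participants, or any other subgroup, benefit more. The algebra needs only randomisation with 1:1 allocation. The simulated rates rest on assumed slopes, and the detectable differences on complete data, an outcome SD of 1 and an assumed depressed share. Dropout, which the article expects, would reduce power further; adjustment for baseline would recover some.

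Severity is moderate. A declared secondary question is left without a valid stated analysis, and a misleading claim about depressed workers is possible. The primary comparison and the sample size of 354 are unaffected.

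**What to change.** Replace the method clause with wording to this effect:

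> Moderation of the intervention effect will be tested by the interaction of randomised group with the covariate, in a model that also contains the group and covariate main effects, for baseline CES-D, age, gender and education. Within the repeated-measures model the test is group × time × covariate, with all lower-order terms. Interaction estimates will be reported with 95% confidence intervals as exploratory.

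Naming a single lead moderator, or reporting effects within CES-D bands, is a matter of preference and is not needed to cure the fault.

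The cost is a sentence or two. The covariates are already to be collected, so no data, sample size or procedure changes. The downside is low power, as shown above: intervals will be wide, and a non-significant interaction should not be reported as evidence that depressed and non-depressed participants benefit equally.
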